#### Statistical Analysis: Specific Objectives

##### Elastic Net Regression Modeling

We will employ penalized regression models to predict baseline self-report outcomes for well-being and mental health. Specifically, for each of the following outcome measures—the World Health Organization-5 Well-being Index (WHO-5) total score, the EPOCH Measure of Adolescent Well-Being total score, the K-CAT Depression Scale total score, and the UCLA Loneliness Scale total score—we will train an Elastic Net regression model using device usage features as predictors. To identify statistically significant predictors for each outcome, we will examine the coefficient estimates of the final trained model. Features with nonzero coefficients after Elastic Net regularization will be considered important predictors and explored further in post hoc analyses.

This approach will enable us to identify which specific aspects of smartphone usage are most strongly and statistically significantly associated with self-reported measures of well-being and mental health at baseline, directly addressing specific aim 1. Furthermore, by examining the patterns of significant predictors across the different outcome variables, we can gain insights into whether time- or content-based engagement metrics are differentially associated with well-being, contributing to specific aim 2. Additionally, by including potential moderators, we can begin to address specific aim 3.

The Elastic Net is a linear regression model that combines the penalties of both Lasso (L1) and Ridge (L2) methods. This approach is especially well-suited for data sets with many potentially correlated predictors, as it simultaneously performs variable selection—shrinking coefficients of irrelevant predictors to zero—and manages multicollinearity.

We consider an initial set of 21 features derived from device usage within the first 2 weeks of the study, proximate to the baseline outcome measures. Given the richness of the device usage data, there is no clear upper limit to the number of features that could be developed. However, 21 features were selected based on initial interest, divided between time-on-device metrics and content-specific engagement, in line with specific aim 2. Additional features such as age, gender identity, household income, and racial and ethnic background will be included to address specific aim 3.

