For each outcome variable, the Elastic Net model will be trained using 10-fold cross-validation. This robust method partitions the data into 10 equally sized folds. The model is trained on 9 folds and evaluated on the remaining fold, repeating the process 10 times so that each fold serves as the validation set once. This procedure provides a reliable estimate of the model’s generalization performance and helps mitigate overfitting. During cross-validation, we will systematically sweep across a grid of Elastic Net hyperparameters: the mixing parameter (α), which controls the balance between L1 and L2 penalties (ranging from 0 to 1), and the regularization strength (λ), which scales the overall penalty. The optimal hyperparameters will be selected based on the mean squared error performance across the 10 validation folds. After identifying these optimal values through cross-validation, the Elastic Net model will be retrained on the entire data set. The resulting model will provide coefficient estimates for each of the 21 device usage features and other moderating features (age, gender identity, etc) in predicting the respective well-being or mental health outcome. To test for moderation, these additional features and their interaction terms will be included as independent variables in the Elastic Net model during fitting. Variables with nonzero coefficients will be considered significant, and their effects on the dependent variables (scores from the WHO-5, EPOCH, K-CAT, etc) will be further investigated by comparing models with and without these moderating factors.

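### Aim 1 appears to be read from the same Elastic Net that holds the moderator interactions, so where moderation exists the usage coefficients and their selection depend on a coding the article does not state

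*Protocol article*

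**What the plan says.** All of the relevant text is in the protocol article under Elastic Net Regression Modeling.

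- For each of WHO-5, EPOCH, K-CAT Depression and UCLA Loneliness, "we will train an Elastic Net regression model using device usage features as predictors".
- The rule for inference is: "To identify statistically significant predictors for each outcome, we will examine the coefficient estimates of the final trained model". The article says this will show which aspects of use are "statistically significantly associated with self-reported measures of well-being and mental health at baseline, directly addressing specific aim 1".
- The predictors are described thus: "We consider an initial set of 21 features derived from device usage within the first 2 weeks of the study". Person factors follow: "Additional features such as age, gender identity, household income, and racial and ethnic background will be included to address specific aim 3".
- After tuning by 10-fold cross-validation and refitting on all data, "The resulting model will provide coefficient estimates for each of the 21 device usage features and other moderating features".
- On moderation: "To test for moderation, these additional features and their interaction terms will be included as independent variables in the Elastic Net model during fitting".
- A nonzero coefficient counts as significant. Variables that pass are then examined further by comparing models that include the moderators with models that leave them out.

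The article states no coding, reference level or centring for the person factors. Under Anticipated Findings it expects the associations to depend on factors such as age, race and gender.

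**The concern.** Aim 1 asks for the strength and direction of the association between measured use and well-being. In a model with usage-by-moderator products, the usage coefficient answers a narrower question: what is the slope when every moderator equals zero? With indicator coding that means one gender and one racial or ethnic group. With uncentred age it means age 0, in a study of children aged 8 to 17.

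In ordinary regression this affects only interpretation, because recoding leaves the fit unchanged and the average slope can be recovered. A penalised fit is not invariant to recoding. The coding can therefore also change which coefficients reach zero, and being nonzero is the article's significance rule. The moderation that the investigators expect is the condition under which this matters. At stake is whether a feature such as screen time is reported as associated with well-being at all.

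**Working it through.** **The plan's own figure.** The Sample Size section gives N=160 for 21 predictors, f²=0.15 and 80% power. The overall F test (u=21, v=N-22, noncentrality f²N, alpha 0.05 assumed) gives power 0.802 at N=160, so the figure reproduces. It covers 21 main effects and has no bearing on the coding question.

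**Algebra.** Take one usage feature x and a gender indicator G, with y = b0 + b1·x + b2·G + b3·x·G. The slope in group G is b1 + b3·G. Assume slopes of 0 in boys and -0.30 in girls, split 50:50, so the average is -0.15.

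- Boys as reference: b1 = 0, b3 = -0.30.
- Girls as reference: b1 = -0.30, b3 = +0.30.
- Centred (G = ±0.5): b1 = -0.15, b3 = -0.30.

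These are the same fitted lines. Their L1 cost differs. With SD(x) = 1, the product column has SD √0.5 = 0.707 under indicator coding and 0.5 when centred. On standardised columns the L1 sums are:

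- Boys as reference: 0 + 0.30×0.707 = 0.212.
- Girls as reference: 0.30 + 0.212 = 0.512.
- Centred: 0.15 + 0.30×0.5 = 0.30.

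The penalty therefore treats identical associations differently according to coding.

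**Simulation, one usage feature.** N=1000, binary gender, age 8-17, slopes 0/-0.30, residual SD 1, 60 data sets, 10-fold cross-validated Elastic Net on standardised columns.

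| Model | Least-squares mean | Elastic Net mean | Nonzero |
|---|---|---|---|
| No interactions | -0.149 | -0.128 | 100% |
| All moderators centred | -0.149 | -0.130 | 100% |
| Zero-slope gender as reference, age centred | 0.003 | -0.008 | 38% |
| Other gender as reference, age centred | -0.300 | -0.270 | 100% |
| Zero-slope gender as reference, raw age | -0.001 | -0.008 | 37% |
| Other gender as reference, raw age | -0.304 | -0.249 | 95% |

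With raw age the least-squares SD rises from about 0.05 to about 0.15, because the coefficient is then extrapolated to age 0.

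**Simulation, full feature set.** 21 features with pairwise r=0.3, two genders, four race groups, age and income. That is 6 moderator columns and 21 + 6 + 21×6 = 153 columns in all. Slopes are again 0/-0.30. Two sets of runs (25 and 48 data sets at N=1000; 40 and 48 at N=300) gave these shares with screen time nonzero:

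- N=1000: boys as reference 8% and 8%; girls as reference 100% and 94%; no interactions 96% and 100%; sum-to-zero coding (second set only) 98%.
- N=300: boys as reference 17% and about 15%; girls as reference 50% and 48%; no interactions 50% and 65%; sum-to-zero coding (second set only) 58%.

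**Sensitivity to the strength of moderation.** 21 features, N=1000, average slope held at -0.15. Share nonzero with the weaker-slope group as reference versus the stronger-slope group, in two sets of runs:

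- 0/-0.30: 17% versus 100%; 13% versus 100%.
- -0.05/-0.25: 53% versus 97%; 53% versus 100%.
- -0.10/-0.20: 90% versus 95%; 93% versus 100%.
- No moderation (one set): 100% versus 97%.

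Sum-to-zero coding gave 93-100% in both sets, and so did the model without interactions where it was run.

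The slopes, SD, group split and correlations are assumptions. The article gives none of them.

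**The case against.** **The coding is not stated.** A reader might infer that every usage coefficient will be the slope in an arbitrary reference group. The document does not support that. It nowhere says that indicator coding or uncentred covariates will be used, and an analysis plan could fix this. With all moderators centred, the single model gave -0.130 against -0.128 without interactions. Where an interaction is absent or shrunk to zero, the coefficient is not group-specific. This part of the objection stands.

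**A single model is not the only reading.** The section first describes a model with usage features as predictors, ties that approach to Aim 1, and brings in moderators as an addition for Aim 3. A base model plus an extension is possible. But the refitted model is said to give coefficients for usage and moderating features together, and the interactions go into the Elastic Net model with no second model named. The single-model reading is the natural one, though not the only one.

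**Models without moderators are foreseen.** They are, but as follow-up of variables already found nonzero. A usage feature removed by the coding is not carried forward, so this does not cure the problem.

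**The study is exploratory.** Selected features go to post hoc work, and no data collection is affected. This limits the severity.

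**Conclusion.** The concern holds in a limited form. The article most naturally reads Aim 1 from a model that also contains the interactions, and does not say at what moderator values the usage coefficients apply. Where moderation is present and the moderators are not centred, size and selection depend on coding.

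The consequence scales with the moderation. It is large if one group has no association. It is modest for selection at N=1000 if slopes differ twofold, although the shrunken coefficients still differ by reference group. It is essentially nil without moderation. A reader who takes only the zero-slope case would overstate the problem.

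These sizes rest on assumed slopes averaging -0.15 and on two gender groups, whereas the study also enrols nonbinary youth. This should be fixed before modelling because the remedy is better and nearly free, but it does not invalidate the study.

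**What to change.** In Elastic Net Regression Modeling, state that Aim 1 is answered from an Elastic Net containing the 21 usage features and the person-factor main effects, with no interaction terms. State that the interaction model is fitted separately and used only for Aim 3, with age and income centred and gender and race/ethnicity sum-to-zero coded, so that no reference level drives selection.

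Centring within a single model would remove most of the dependence. However, sum-to-zero coding gives equal weight to groups of unequal size, so the main-effects model is the more direct answer to Aim 1.

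The cost is about two sentences and one extra model fit per outcome, four in all. No new data are needed.

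### A nonzero Elastic Net coefficient is labelled statistically significant, although the selection has no type I error rate and the tuning range includes pure ridge

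*Protocol article*

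**What the plan says.** All of the following is in the protocol article, under Elastic Net Regression Modeling.

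- **Purpose.** "To identify statistically significant predictors for each outcome, we will examine the coefficient estimates of the final trained model". The next paragraph says the approach will show which aspects of use are statistically significantly associated with the four baseline outcomes (WHO-5, EPOCH, K-CAT Depression, UCLA Loneliness).
- **Rule.** "Variables with nonzero coefficients will be considered significant". A softer sentence in the same section reads: "Features with nonzero coefficients after Elastic Net regularization will be considered important predictors and explored further in post hoc analyses".
- **Tuning.** "The optimal hyperparameters will be selected based on the mean squared error performance across the 10 validation folds". The mixing parameter is described as one "which controls the balance between L1 and L2 penalties (ranging from 0 to 1"). The lambda grid is not given. After tuning, "the Elastic Net model will be retrained on the entire data set".
- **Moderation.** "To test for moderation, these additional features and their interaction terms will be included as independent variables in the Elastic Net model during fitting". The moderators are introduced thus: "Additional features such as age, gender identity, household income, and racial and ethnic background will be included to address specific aim 3". The nonzero rule applies to them too, followed by a comparison of models with and without them, for which no criterion is given.

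**The concern.** Calling a result statistically significant claims a known, small chance of being wrong when there is no effect. A coefficient that survives a penalty tuned for prediction error carries no such guarantee. Minimum-error tuning tends to keep weak and null variables, because retaining them costs little in prediction.

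The section also undercuts its own rationale. It justifies Elastic Net because irrelevant predictors are shrunk to zero, yet one end of the 0-to-1 mixing range is pure ridge under either coding of the parameter. If cross-validation picks ridge, every feature, moderator and interaction counts as significant.

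At stake are the lists of usage features and moderators that the first publication would present as statistically significant, on a publicly contested question.

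**Working it through.** **1. The plan's own figure.** Sample Size assumes R² = 0.13, f² = 0.15, 21 predictors and 80% power, and gives N = 160. No alpha is stated, so 0.05 is assumed. Conversion: f² = 0.13 / (1 − 0.13) = 0.149. For the overall F test with u = 21, v = N − 22 = 138 and noncentrality f²·N = 0.15 × 160 = 24, power is 0.802 (0.800 with f² = 0.13/0.87). The figure of 160 reproduces. It powers the overall test that R² exceeds zero and says nothing about single nonzero coefficients.

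**2. Simulating the rule under R² = 0.13.** From the documents: 21 features, 10-fold cross-validation, minimum mean squared error, refit on all data, nonzero = significant. Assumed: normal features with equal pairwise correlation r, and R² carried by 5 features, leaving 21 − 5 = 16 null. The mixing grid was 0 to 1 in steps of 0.25, then the same grid without ridge (for the r = 0.3 rows, 0.1 replaced 0). There were 600 runs per setting for r = 0.3 and 200 otherwise.

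| r | N | Null features nonzero, ridge allowed | Null features nonzero, ridge excluded | At least one null feature, ridge excluded |
|---|---|---|---|---|
| 0 | 160 | 62% | 33% | 89% |
| 0 | 1000 | 40% | 39% | 99% |
| 0.3 | 250 | 69% | 41% | about 99% |
| 0.3 | 1000 | 46% | 40% | about 99% |
| 0.6 | 160 | 70% | 29% | 99% |
| 0.6 | 1000 | 64% | 36% | 99.5% |

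With ridge excluded, 16 × 0.29 = 4.6 to 16 × 0.41 = 6.6 null features are expected to be called significant per outcome. Unadjusted 5% tests would give 16 × 0.05 = 0.8.

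**3. Moderation.** The article names four moderators without fixing the list or the coding. If each is one column, there are 4 × 21 = 84 interactions. With R² = 0.13 from main effects only, r = 0.3 and ridge excluded (60 runs), 8-9% of null interactions are nonzero. That is 84 × 0.08 = 6.7 to 84 × 0.09 = 7.6 terms, with at least one false interaction in 83% (N = 160) to 93% (N = 1000) of runs. With 9 moderator columns (9 × 21 = 189 interactions), a small run of 35 replicates at N = 1000 gave a mean of 16.6, or 16.6/189 = 8.8%. The proportion is similar, but the count moves with the coding.

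**4. No true effect at all.** With ridge excluded, about 8-10% of null features are nonzero and at least one appears in 37-42% of runs. With ridge allowed, the result depends on how far the lambda grid extends for ridge (N = 1000, r = 0.3, 40 runs each):

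| Largest ridge lambda, relative to the lasso maximum | Ridge chosen | Null features nonzero | At least one |
|---|---|---|---|
| same | 0% | 2.7% | 17.5% |
| 10 times | 12.5% | 16% | 35% |
| 1000 times | 55% | 56% | 67.5% |

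A separate variation of the same setting moved ridge selection from 0% to 84% and false nonzero features from 9% to 86%.

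**5. Comparator with a defined error rate.** Coefficient tests in the 21-feature linear model, Holm-adjusted at 0.05 (2000 runs per setting), gave a chance of any false finding of 0.041 to 0.054. Each true feature was then detected with probability 0.01 to 0.155 at N = 160 and 0.12 to 0.99 at N = 1000, depending on correlation.

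**The case against.** **The label may be only loose wording.** The section also calls nonzero features important predictors for post hoc exploration, and the study is observational. This has some force: much of the fault is cured by changing a word. But statistical significance is claimed in two paragraphs, and neither the post hoc work nor the with/without comparison has a criterion or independent data. The exploratory language sits under Additional Possible Analytic Approaches, which covers work beyond the specific aims.

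**A separate analysis plan may define the inference.** This stands for what the article merely leaves out: the absence of intervals and of a multiplicity procedure is not in itself the finding. It does not cover a decision rule that the article states and states wrongly.

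**Stronger readings that the documents do not support.**

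- A reader might infer that with no true effect about 80% of null features, and nearly every analysis, would be false findings. That holds only for some lambda grids, and the grid is not given. The ridge coefficients involved can be tiny (median about 0.003 SD at the widest grid in the step 4 table).
- A reader might compound the error across the four outcomes as if they were independent. They are well-being and distress scores from the same children, so independence is implausible.
- A reader might say that all three aims are decided by this rule. The section ties aim 1 to it directly, but says only that it contributes to aim 2 and begins to address aim 3.
- A reader might blame ridge alone. In the 84-interaction model at N = 1000 with R² = 0.13, ridge was chosen in 2% of runs, and false interactions were still common.

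**Conclusion.** The rule is wrong as written. Nonzero after tuning for prediction error is a selection, not a significance test, and reading selection from zeros is incompatible with a mixing range that includes ridge.

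Under the protocol's own R² = 0.13, roughly 30-40% of null features would be called significant even with ridge excluded, with at least one in nearly every run. About 8-9% of null interactions would be, with at least one in most runs. These figures assume 5 true features, equal feature correlation (about 0.3 centrally; 0 and 0.6 also tried for the features) and one column per moderator; the number of false moderators changes with that coding. With no true effect, only a range can be given, from about 3-9% to over 80% of null features, because the lambda grid is not stated. No combined figure over the four outcomes is warranted.

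**What to change.** 1. In both places in the Elastic Net section, call variables with nonzero coefficients selected, not significant.
2. Exclude the ridge endpoint from the mixing grid if selection is read from zeros, and state the lambda grid. This alone does not cure the problem, as steps 2 and 3 of the working show.
3. Base any significance statement, for features and for interactions, on a separate procedure with a defined error rate and 95% confidence intervals. Options are a prespecified regression, a debiased Elastic Net, or stability selection with an error bound. Control multiplicity across features and the four outcomes, and separately across the moderator tests.
4. Before fitting any unpenalised regression, remove redundant features. The list has total, daytime and nighttime screen time, which are exactly collinear if day and night add up to the total (an assumption), and it appears to list session length twice. A regression on all 21 as listed could leave coefficients unstable or not estimable.

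The cost is wording, some analysis work, and fewer features declared significant. The detection probabilities in step 5 show that this price is steep at N = 160 and much lower near N = 1000 unless features are strongly correlated. The article places the initial analysis in late autumn 2025 or winter 2026, and the change belongs before it.

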### Statistical Considerations

#### Specific Aims

Three specific aims will be initially addressed in this work (Textbox 1).

Specific aims.Quantify the associationDetermine the strength and direction of associations between objectively measured smartphone use (eg, total screen time, frequency of use, specific app engagement) and self-reported well-being measures (eg, Kiddie Computerized Adaptive Testing [K-CAT], World Health Organization-5 Well-being Index [WHO-5]).Differentiate engagement typesEvaluate whether distinct aspects of smartphone engagement—specifically, the types of content consumed versus overall time spent on the device—show differential associations with well-being outcomes.Identify moderating factorsInvestigate the extent to which key person-centered characteristics, including age, gender identity, and socioeconomic status, moderate the relationships observed between smartphone usage and well-being.

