##### Sample Size

The initial target enrollment for the study is 1000 participants with complete data for baseline and months 1-3. While we aim to explore a wide range of outcomes related to digital device usage and mental health, our initial analysis will focus on the specific aims outlined above.

To assess the appropriateness of this sample size for powering the planned analyses, we consider our initial set of 21 features. For a multiple regression model (of which Elastic Net is an extension), assuming a moderate effect size (*R*^2^=0.13, Cohen *f*^2^=0.15) between a well-being measure and 21 device usage–based predictors, a sample size of 160 participants is required to achieve 80% power. Our goal in enrolling additional participants in this ongoing study is to enable more fine-grained analyses of other research questions and to provide a resource for qualified investigators to explore a wider range of analyses (see the “Data Sharing” section).

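### Neither step stated for Aim 3 isolates moderation: any nonzero Elastic Net coefficient counts as significant, and the follow-up comparison appears to remove main effects together with interactions

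*Protocol article*

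**What the plan says.** Aim 3 (Protocol article, Specific Aims) asks whether age, gender identity and socioeconomic status "moderate the relationships observed between smartphone usage and well-being". The method is under Elastic Net Regression Modeling:

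- Usage predictors: "We consider an initial set of 21 features derived from device usage within the first 2 weeks of the study".
- Moderators: "Additional features such as age, gender identity, household income, and racial and ethnic background will be included to address specific aim 3".
- Tuning: "The optimal hyperparameters will be selected based on the mean squared error performance across the 10 validation folds".
- Fitting: "To test for moderation, these additional features and their interaction terms will be included as independent variables in the Elastic Net model during fitting".
- Decision rule: "Variables with nonzero coefficients will be considered significant".
- Follow-up, in the same sentence as the decision rule: the effects "will be further investigated by comparing models with and without these moderating factors".

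The outcomes modelled are the totals of the WHO-5, EPOCH, K-CAT Depression and UCLA Loneliness scales. The article does not say which interactions are formed, or what the model without the moderating factors still contains.

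**The concern.** A factor moderates the usage–outcome relation only if its interaction with usage is nonzero. Two features of the stated procedure blur this.

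1. The decision rule applies to variables in general and attaches no error rate to them. Minimum cross-validated error selects for prediction and usually lets in some noise terms. Nothing in the rule limits how many null interactions are then called significant.
2. The follow-up compares models with and without the moderating factors. Earlier in the same paragraph, moderating features means age, gender identity and so on, that is, the variables themselves. If they are removed, their main effects go too. A factor that merely predicts well-being then makes the fuller model look better.

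Age, gender and income may well have main effects on these outcomes. At stake is a report that device use acts differently by age, gender or income when those factors only shift the outcome level.

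**Working it through.** **The plan's own figure.** The Sample Size section gives 160 participants for 80% power, "assuming a moderate effect size" (f² = 0.15) with 21 predictors. Taking alpha = 0.05 (not stated): u = 21, v = 160 − 22 = 138, noncentrality = 0.15 × 160 = 24, power = 0.802. The figure reproduces. It concerns the overall R² of the 21 usage features, contains no interaction, and so neither supports nor undermines the moderation step.

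**Number of terms (assumed full crossing).** One moderator: 21 × 1 = 21 interactions. Four single-column moderators: 21 × 4 = 84.

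**Simulation settings (assumptions, not from the documents).** No true interaction in any run; 10-fold, minimum-error Elastic Net; pure ridge left out of the grid, since it zeroes nothing.
- Setting A: age only, correlated 0.3 with the outcome, no usage effect. Ranges cover independent repeats.
- Setting B: four moderators, two of them with main effects of 0.20–0.25, and two usage features with effects of similar size; 60 runs per n.

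| Result with no true interaction | A, n=160 | A, n=1000 | B, n=160 | B, n=1000 |
|---|---|---|---|---|
| At least one interaction nonzero | about 70% | about 70% | 97% | 98% |
| With-moderator model has lower cross-validated error than without | 93–100% | 100% | 78% | 100% |
| Joint F test (main effects and interactions dropped together) rejects | 43% | 100% | 13% | 100% |
| Interaction-only F test rejects | about 5% | about 5% | 7% | 8% |

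The about 70% in A summarises repeats from 60% to 76%. With 60 runs the Monte Carlo standard error at 5% is √(0.05 × 0.95/60) = 2.8 points, so 7–8% is compatible with 5%.

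**Rate per term.** At n = 160, one run of A kept 2.6 false interactions of 21 (2.6/21 = 12%), and B kept 10.35 of 84 (12%). No parameter in the plan sets this rate.

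**Closed-form check of the joint test in A.** f² = 0.09/0.91 = 0.099. The block has 1 + 21 = 22 terms and the full model 43, so v = n − 44. Noncentrality ≈ 0.099 × (n − 22).
- n = 160: about 13.6, v = 116, power about 0.46, in line with the simulated 43%.
- n = 1000: about 96.7, v = 956, power above 0.999.

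This rejection comes entirely from the main effect of age. If the reduced model keeps age, the same data give a cross-validated preference for the fuller model in 20–26% of runs, and an F test near its nominal level.

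**Interactions without main effects.** In A, roughly 60% to 77% of the false interactions were kept while the usage feature's own main effect was zero (for example 2.2 of 3.6, and 1.7 of 2.2). Since Z(M − c) = ZM − cZ, such a coefficient changes with the centring of the moderator M and partly stands in for the main effect of the usage feature Z. It is not a clean measure of moderation.

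**The case against.** The strongest answer is the sentence just before the follow-up. Interactions are entered expressly to test for moderation, with coefficients separate from the main effects, and the with/without comparison comes only afterwards. This stands. A reader might infer that moderation is decided by the with/without comparison, or that the plan cannot separate a main effect from an interaction. The text supports neither. The 93–100% figures therefore describe a secondary step, judged by which model predicts better with no threshold. They are not the error rate of Aim 3.

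Second, the reduced model is not defined, and the phrase could mean removing only the selected interaction terms. That is possible, though the paragraph's own use of moderating features points to the variables. If only interactions are meant, one added clause settles it, and the nonzero rule still needs correction.

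Third, the nonzero rule affects the 21 usage features as well. True, but it is also the only stated decision rule for interactions.

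Fourth, penalty factors, centring and hierarchy are normally left to the analysis plan. Agreed: the article mentions one overall penalty strength and no more, so interactions without main effects are a possible consequence and not a stated choice.

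Fifth, the modelling section says only that including moderators begins to address Aim 3, and the later section on possible analyses calls the study exploratory. This lowers the stakes. But the Introduction lists moderation among three primary aims, and the rule uses the word significant.

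**Conclusion.** The point holds in limited form. The model contains the coefficients needed to study moderation, but the rule for reading them has no error control, and the follow-up as most naturally read mixes main effects with moderation. Neither step, as stated, is a test of moderation.

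Under the assumed settings, about 70% of analyses with one moderator, and 97–98% with four, keep at least one false interaction. At n = 1000 the with/without comparison favours the moderator model every time on the strength of a main effect alone. At n = 160 the result depends on the criterion and setting: 13% or 43% by a joint F test, 78% to 100% by cross-validated error. An interaction-only test stays close to 5%.

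These sizes rest on assumed main effects, feature correlations and full crossing of moderators with usage features. A reader might go further and conclude that Aim 3 will report false moderators. The documents do not support that certainty: true interactions may exist, the number of terms is not fixed, and the investigators may read the follow-up as removing interactions only.

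**What to change.** State the moderation test as a comparison of two nested models for each moderator: (a) usage features plus moderator main effects; (b) the same model plus that moderator's interactions with the usage features. Main effects stay in both. Test the block with an F test, or with a permutation test that permutes residuals from model (a).

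Control multiplicity across moderators and outcomes. With the four named moderators and four outcomes there are 4 × 4 = 16 block tests; unadjusted and if independent, the chance of at least one false positive is 1 − 0.95¹⁶ = 56%. Bonferroni would use 0.05/16 = 0.0031, and Holm is less strict.

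Treat nonzero interaction coefficients from the Elastic Net as screening only, and do not call them significant. Report simple slopes with intervals for blocks that pass. Define the model without moderating factors as the one without their interaction terms. Leaving main effects unpenalised is one way to keep them in; a hierarchical lasso is another.

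The cost is wording and code, with no new data or participants. The downside is that fewer moderators will be claimed.
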